### Data monitoring

This RCT study has been designed for conciseness and minimizing risk. Therefore, no formal data monitoring committee has been organized. In addition, no interim analysis of the intervention’s impact has been planned at this stage.

### Ethics

During the post-training session, participants of the experimental group will have a debriefing with the research psychologist. Should any participants experience adverse emotional reactions after the session, they will be addressed to appropriate psychological support, and the possibility of withdrawal from the study will be considered. These events will be recorded. Specifically, the time point at which the adverse events occurred, the motivation, and the events’ features (which emotions and with which intensity, which psychophysiological perceptions) will be collected and recorded on the CRF. Any adverse event will be discussed within the project team and assessed individually to identify any variable needing revision within the virtual content. If any substantial protocol modifications are needed because of organizational and/or clinical reasons, the study will be promptly suspended.

### Auditing

No audit has been planned at this time.

### Protocol amendments

Protocol amendments, including informed consent for participants, will be sent to the ethical committees for evaluation. Once the amendments are approved, a modified informed consent form will be given to participants and signed.

### Access to data

Prior to the publication of major results, only the study coordinator and individuals approved by the study coordinator will have access to the complete dataset. They will address problems related to the data and finalize a dataset for statistical analysis. After publication, the dataset created during this study will be available from the study coordinator on reasonable request.

### Ancillary and post-trial care

The study does not involve any physical, psychological, or social risks. Participants will be able to contact the research psychologist during the trial period. The study could be stopped if any adverse effects related to the use of VR (i.e., nausea, vertigo) will be reported by the participant during the intervention.

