### Withdrawn criteria

Participants will be considered withdrawn if any of the following occurs: (1) participant chooses to withdraw from the study at any time, (2) intolerable adverse effects, (3) major violation of the study protocol, and (4) other circumstances that would endanger the health of the subject if he/she were to continue his/her participation in the trial. The date and reason for withdrawal will be documented in a paper-and-pencil case report form (CRF).

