#### Secondary outcome measure

Participants in the experimental group at post-intervention will complete the following questionnaires that will serve as the secondary outcome measures: *System Usability Score (SUS) *[82]*:* it consists of 10 items on a 5-point Likert scale (1= “strongly agree,” 5= “strongly disagree”), relating to the possible critical issues encountered during the use of a VR system. A measure is provided on usability aspects (i.e., efficiency, clarity, reliability) and other aspects of the user experience (i.e., originality, stimulation).*Subjective Difficulty Measure (SDM):* it consists of a horizontal line 100 mm long, anchored by word descriptors at each end (from “not at all” to “very much”). Users mark on the line the perceived difficulty in using the VR system in general, MIND-VR, and The Secret Garden.*Net Promoter Score (NPS) *[83]: it evaluates user satisfaction with a product, in this case: the VR-home-based intervention in general, MIND-V, and The Secret Garden. It requires to indicate on a scale from 0 (“not at all”) to 100 (“very much”) how much they would recommend the products to a family member or friend.*Ad hoc questionnaire on difficulties and adverse effects*: individuals are asked to rate on a 7-point Likert scale (1=“not at all,” 7 = “very much”): If they had difficulty following the experimental protocol; if they had nausea, headache, dizziness, and eyestrain while using the VR system in general; if they had nausea, headache, dizziness, and eyestrain while using MIND-VR; if they had nausea, headache, dizziness, and eyestrain experienced while using The Secret Garden.

Furthermore, adherence to study protocols will be assessed through data on VR usage recorded on the log book, training sessions completed, assessments attended, and drop-outs. Data recorded by participants on the log book regarding technical problems and safety issues will serve to evaluate the usability of the VR system.

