Finally, during the post-training session, participants of the experimental group will be interviewed for about 15 min. The questions will be based on the methodology used in a recent study [51]: Were there any features that you especially liked in using the home-based VR training? Were there any features you did not like or found useless? Have you ever had to stop using VR, and if so, why? Have you learned anything using MIND-VR and The Secret Garden? Were there any features of the VR experiences more valuable than others? Would you like to have more sessions with this type of training? Do you have any questions or would like to add anything?

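### Intolerable adverse effects count as withdrawal rather than as the end of VR training, so outcome data may be lost in the VR arm only; the no-risk sentence also needs correcting

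*Protocol article*

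**What the plan says.** The section Withdrawn criteria opens with "Participants will be considered withdrawn if any of the following occurs" and lists four events. The second is "intolerable adverse effects". The first is the participant's choice to leave the study, and the fourth is danger to health from continuing in the trial. The date and reason go on the case report form. The section has no separate category for someone who ends the training but stays under assessment.

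Under Ethics, after an adverse emotional reaction, "the possibility of withdrawal from the study will be considered". The section Control group says that controls are assessed at the same times but have no training.

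The primary questionnaires are due at baseline, week 1 and week 5 (Table 2). The adverse-effects questionnaire is a secondary outcome, completed only by the VR arm and only after the intervention. It asks, for example, "if they had nausea, headache, dizziness, and eyestrain while using the VR system in general", and repeats the question for each of the two VR contents.

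On risk, Ancillary and post-trial care states: "The study does not involve any physical, psychological, or social risks".

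**The concern.** Ending a treatment and leaving a trial are different events. A person who cannot tolerate the headset can still fill in online questionnaires at weeks 1 and 5. The withdrawal list merges the two for exactly the people whose data say most about tolerability.

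One of the two arms has no VR to tolerate. Any loss through VR-caused effects therefore depends on the arm and on how the person responded to the intervention. Two results are exposed:

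- the comparison of stress and anxiety scores between the arms, if those who tolerated VR worst also improved less (or more) than the rest of their arm;
- the acceptability results, because the side-effect ratings would then come mainly from people who tolerated VR.

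The no-risk sentence is a separate and smaller matter. It does not fit a trial that measures side effects and plans referral for emotional reactions.

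**Working it through.** **1. What withdrawn means.** The list does not say in so many words that data collection stops. Criterion 1 speaks of leaving the study and criterion 4 of participation in the trial; Ethics also speaks of withdrawal from the study. Read beside these, criterion 2 most naturally takes the person out of the study, not only out of the training.

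**2. Who can meet criterion 2 through VR.** Allocation is 1:1 with 60 participants, so 30 per arm. Controls have no training. Exposed to this route: 30 of 30 in the VR arm, 0 of 30 controls. The criterion is worded for both arms; the asymmetry comes from the untreated control.

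**3. What would be lost.** The week-1 and week-5 primary scores, and the week-1 adverse-effects questionnaire. The latter covers 4 symptoms (nausea, headache, dizziness, eyestrain) × 3 settings (VR in general, MIND-VR, The Secret Garden) = 12 ratings. The planned 2 × 2 mixed ANOVA (group × pre/post) needs the week-1 score.

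**4. How a loss would act.** Let p be the fraction of the VR arm lost, O the mean change in those observed and L the mean change in those lost. The full-arm mean is (1 − p)O + pL, so the observed mean is off by O − [(1 − p)O + pL] = p(O − L). The document gives neither p nor O − L. As an illustration only: if the whole drop-out reserve came from the VR arm, p = 6/30 = 0.20, and the error would be one fifth of the difference between stayers and leavers. It is zero if the two do not differ.

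**5. Power.** The planned N is reproduced first. For the group × time interaction with f = 0.25, 2 groups, 2 time points, two-sided alpha 0.05 and correlation ρ = 0.5 (assumed; not stated in the document), λ = f² × N × 2/(1 − ρ), with 1 and N − 2 degrees of freedom. For unequal groups, N in λ is replaced by 4·n₁·n₂/(n₁ + n₂).

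| Group sizes | N used in λ | λ | Power |
|---|---|---|---|
| 27 + 27 (planned N = 54) | 54 | 0.0625 × 54 × 4 = 13.50 | 0.950 |
| 30 + 30 (enrolled) | 60 | 15.00 | 0.968 |
| 24 + 30 (all 6 spare lost from VR arm) | 4 × 24 × 30/54 = 53.3 | 13.33 | 0.948 |

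The reserve is 60 − 54 = 6. Losing all of it from one arm costs almost no power. What matters is which people are lost.

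**6. The no-risk sentence beside the rest of the document.**

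| Kind of risk | What the document provides for |
|---|---|
| Physical | nausea and vertigo, two sentences later in the same section; intolerable effects as a withdrawal criterion; four symptoms rated as a secondary outcome |
| Psychological | adverse emotional reactions, with referral and possible withdrawal (Ethics) |
| Social | nothing found that contradicts the sentence |

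**The case against.** **The loss of data is inferred from silence.** The withdrawal section does not say that questionnaires stop. Under the section on adherence, the psychologist phones those who miss questionnaires, with no stated exception for withdrawn participants. Follow-up after withdrawal is often left to a fuller protocol or analysis plan. This stands in part: the consequence is conditional. But the criterion itself is a stated rule, and its natural reading takes these people out of the study.

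**Safeguards exist.** There is a log book, adverse events go on the case report form, "Any adverse event will be discussed within the project team and assessed individually", and those who drop out are compared with those who stay. These limit the loss of safety information. They do not replace missing stress and anxiety scores.

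**The protocol may already expect such people to stay.** The post-training interview asks "Have you ever had to stop using VR, and if so, why". That question fits a short pause within a session equally well, so it is weak evidence either way.

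**The no-risk sentence has no operational effect.** This stands: no procedure relies on it, and correcting it is a matter of wording.

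**A stronger reading concerns the stop sentence.** A reader might infer from "The study could be stopped if any adverse effects related to the use of VR (i.e., nausea, vertigo" that one report of nausea would stop the trial, or that the sentence conflicts with the withdrawal criteria. The document does not support this. The wording is permissive and refers to a report by a single participant, and Ethics already provides for individual review and for suspension. What is left is detail that an article may leave to the full protocol.

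**Conclusion.** The point holds as a minor one. The withdrawal rule, as worded, treats intolerance of the intervention as leaving the study, and for VR-caused effects that route exists in one arm only. Outcome and side-effect data from those who tolerated VR worst may therefore be missing from that arm. This assumes that withdrawn is applied as out of the study. The size is unknown, since no event rate and no outcome difference between stayers and leavers is given. Sample size is not threatened, under the assumed correlation of 0.5.

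Two further inferences are tempting but not supported. A reader might conclude that the trial's result will be biased; the document shows only a route by which it could be. A reader might also conclude that participants were told there is no risk; the consent text is not available, so this cannot be judged. The contradiction in the no-risk sentence covers physical and psychological risk, not social risk.

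**What to change.** **Withdrawn criteria.** Replace criterion 2; adding a sentence beside it would make the section contradict itself. Suggested text: *Intolerable adverse effects lead to ending VR training, not to withdrawal from the study. These participants are still asked for the week-1 and week-5 questionnaires, including the adverse-effects questionnaire at week 1, unless they withdraw consent or criterion (4) applies.* Keep them in the analysis in the arm to which they were randomised. Criterion 4 still protects anyone for whom continuing would be harmful.

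**Ancillary and post-trial care, first sentence.** Suggested text: *Expected risks are low; temporary nausea, headache, dizziness, eyestrain and adverse emotional reactions are possible.* Check that the consent text agrees. The stop sentence needs no change on account of this point.

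**Cost.** A few more reminders, and an amendment to the ethics committees. Under Protocol amendments, a modified consent form would be signed, so people already enrolled may have to sign again. The first change alters a rule and should be filed as such. Ethics provides for suspending the study when substantial modifications are needed, so the sponsor should settle with the committees beforehand whether this one counts. Eligibility, randomisation, sample size and questionnaires do not change.

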### Dissemination plans

The study outputs and methodology will be disseminated worldwide to professionals and researchers to promote the exploitation of project findings in future confirmatory studies and in recommendations for the management of healthcare professionals’ mental health. The use of project findings in further studies and replication in other contexts will provide external validity to the results and favor a potential standardization impact.

### Discussion

The main aim of this RCT study is to evaluate the usefulness and the acceptability of a brief home-based VR training for the management of stress and anxiety in healthcare workers. Since stress and anxiety have increased after the outbreak of the COVID-19 crisis [4–7] and given that these conditions can have harmful effects on both health and work performance [17, 18, 20, 21], the study’s findings may offer valuable insights for developing innovative psychological interventions to help hospital staff.

If our brief home-based VR training will produce a significant decrease in stress and anxiety and an increase in the knowledge of these conditions, it could become an empirically assessed viable option for protecting the mental health of healthcare workers both during the pandemic and once the emergency ends. Furthermore, it could easily be adapted to other categories of people who need support in managing stress and anxiety. Indeed, the proposed intervention is characterized by the fact that it uses free and ready-to-use virtual experiences, available in different languages, including English (e.g., MIND-VR and The Secret Graden). For example, the proposed VR intervention can be used within programs to manage stress and anxiety for all those people forced into isolation or an extended hospital stay due to COVID-19 infection or other physical disorders. Also, since Summer 2021, this type of approach has been tested in collaboration with a Canadian university and an Italian hospital, respectively, to train future doctors and nurses and provide psychological support to families of patients with dementia.

In terms of format and content, the brief home-based VR training proposed in this study has many advantages over other VR-based interventions previously tested for managing stress and anxiety of healthcare workers [58, 59]. First of all, to the best of our knowledge, this is the first study to propose the use of VR at home and not in a hospital or laboratory. In our study, healthcare workers will access the VR training directly in their homes and at times that are most convenient for them. Data collected by this study will offer helpful insights on the efficacy and acceptability of VR-based training, which represents an interesting new way to offer remote pisco support and which could facilitate treatment adherence compared to face-to-face VR interventions [61–63]. Importantly, in this study, we will use VR standalone systems, which, compared to other types of immersive systems that are easy to use even at home, such as mobile ones, offer a higher quality experience with more possibilities for interaction. Secondly, unlike previous research [58, 59], the training proposed by this study/protocol involves using VR not only for relaxation but also for psychoeducation on stress and anxiety. As suggested by the literature, this fact appears essential as it could increase treatment adherence and lower self-stigma [66, 67].

This study protocol has some limitations. First of all, a third control arm (i.e., treatment as usual) and the physiological monitoring of individuals will not be possible due to the limitation of cost and feasibility. Secondly, it will not be possible to guarantee that the participants themselves performed the training session or that another individual had replaced them. To date, this drawback is common with most (if not all) home-based training programs. Finally, as healthcare workers who volunteered to participate may have been more stressed and or receptive to a VR intervention, the responses may be susceptible to selection bias.

To summarize, if the data collected will give evidence of the efficacy and acceptability of our brief home-based VR training for managing stress and anxiety, the proposed approach can be implemented quickly and cheaply as add-on treatment or continued care to enhance the effectiveness of current evidence-based interventions for healthcare workers. Besides, the proposed training might be easily adapted for other categories of people who need support in managing stress and anxiety.

### Trial status

Patient recruitment was ongoing at the time of manuscript submission. Data collection will continue at least until March 2023.

## Data Availability

The datasets of the study are available on request from the authors.

## Abbreviations

2D: Two-dimensional
3D: Three-dimensional
CAVE: C-Automatic Virtual Environment
CBT: Cognitive-behavioral therapy
CFT: Compassion Focused Therapy
COVID-19: Novel coronavirus disease
CRF: Case report form
DASS-21: Depression, Anxiety, and Stress Scale-21 Items
FCOR: Fear of coronavirus
FERB: Fondazione Europea Ricerca Biomedica
HMDs: Head-mounted displays
IRBC: Institutional Review Board Committee
MANOVA: Multivariate analysis of variance
NPS: Net Promoter Score
PSS-10: Perceived Stress Scale
PTSD: Post-traumatic stress disorder
RCT: Randomized controlled trial
SDM: Subjective Difficulty Measure
STAI-Y1: State-Trait Anxiety Inventory Form Y-1
STAI-Y2: State-Trait Anxiety Inventory Form Y-2
SUS: System Usability Score
UCD: User-centered design
VAS-A: Visual Analogue Scale for Anxiety
VR: Virtual reality
WHO: World Health Organization
